# A new phototherapy regimen during winter as an add-on therapy, coupled with oral vitamin D supplementation, for the long-term control of atopic dermatitis: study protocol for a multicentre, randomized, crossover, pragmatic trial – the PRADA trial

**DOI:** 10.1186/s13063-019-3276-9

**Published:** 2019-03-25

**Keywords:** Atopic dermatitis, vitamin D, phototherapy, long-term control, add-on therapy, pragmatic trial

## Abstract

**Background:**

Atopic dermatitis is a highly prevalent, chronic, relapsing disease in both adults and children. On the severity spectrum, lower-end patients benefit from small amounts of topical anti-inflammatory treatments (TAT), whereas higher-end patients need systemic immunosuppressants; in-between patients are treated with TAT and phototherapy. The major therapeutic challenge in this population is the long-term control of disease activity, and the current TAT-based pro-active strategy does not meet all their needs. Immunosuppressants are used as long-term control add-on treatments, but they are restricted to the most severely affected patients because of safety concerns. In addition, neither immunosuppressants nor other strategies have been properly evaluated in the long term despite long-term control having been acknowledged as one of the most important core outcome domains to be targeted in atopic dermatitis trials. Safe add-on therapies, rigorously evaluated for long-term control of the disease, are therefore needed. Phototherapy and vitamin D supplementation are both good candidates.

**Methods:**

This is a multicenter, national, randomized, superiority, crossover trial testing add-on phototherapy (one winter under spaced sessions of phototherapy and one winter under observation) among subjects receiving standard care (i.e., TAT). On the same population, we will test the long-term control provided by oral supplementation of vitamin D versus placebo in a randomized, superiority, double-blind, parallel-group trial. The primary outcomes are (1) repeat measures of the PO-SCORAD severity score over 1 year and (2) cumulate consumption of TAT (number of tubes) during the winter. They will be tested following a hierarchical testing procedure. The secondary outcomes will be measures repeated over 2 years of investigator-based severity scores, patient-reported severity and quality of life scores, serum vitamin D levels, weeks during which the disease is well-controlled, inter-visit cumulate consumption of TAT, and synthetic patient-reported satisfaction at the end of each winter.

**Discussion:**

This study includes two separate 2-year pragmatic trials designed to evaluate the efficacy of vitamin D supplementation and pro-active phototherapy for primary care atopic dermatitis patients receiving TAT on long-term control of disease activity. The experimental design enables the study of both interventions and exploration of the interaction between vitamin D and phototherapy. A pragmatic trial is particularly suited to the assessment of long-term control. This study explores the possibility of new and safe therapeutic strategies for the control of long-term atopic dermatitis, and is an example of efficacy research that is unlikely to be sponsored by industrialists. A potentially effective low-cost therapeutic strategy for long-term control is essential for patients and public health.

**Trial registration:**

ClinicalTrials.gov Identifier: NCT02537509, first received: 1 September 2015.

**Electronic supplementary material:**

The online version of this article (10.1186/s13063-019-3276-9) contains supplementary material, which is available to authorized users.

## Background

Atopic dermatitis (AD) is a common pruritic inflammatory skin disease that classically has a chronic course of flares and remissions. AD is a highly prevalent skin disorder, in both adults (2–10%) [1–4] and children (15–20%) [1, 5–7], and there is some evidence of an increase in AD prevalence in some regions of the world, including Western Europe [8]. Children with persistent and/or severe disease have increased AD persistence in adulthood [9].

On the severity spectrum, lower-end patients benefit from emollients and small amounts of topical corticosteroids, whereas higher-end patients need systemic immunosuppressants; in-between patients are treated with topical corticosteroids and tacrolimus (topical anti-inflammatory treatments; TAT) and phototherapy. The management of AD requires efficient control of the flares. TAT are important anti-inflammatory drugs used in AD flares. Topical corticosteroids applied on inflammatory lesional skin are widely used as a first-line treatment for disease flares. They have been evaluated in a wide variety of preparations in more than 110 different randomized controlled trials [10]. Topical calcineurin inhibitors are a second class of TAT drugs that have also proved efficacious against AD flares [11], and are administered alone or in combination with topical steroids. Phototherapy is widely used as a second-line treatment for the short-term control of moderate-to-severe AD with demonstrated efficacy, with intensive schedules of 2–7 sessions a week for 2 or 3 months [12, 13].

These chronic in-between AD patients need large amounts of TAT to maintain control of disease activity. They certainly have the most markedly unmet medical need, with a high impact on quality of life compared to other chronic inflammatory skin diseases [14]. The major therapeutic challenge in this population is the long-term control (LTC) of disease activity, and the current TAT-basedpro-active strategy (intermittent applications of TAT after flares on previously affected skin, over long-term periods) does not meet all the needs. There is also consistent evidence of subclinical inflammation in skin of normal appearance and in the treated skin of AD patients. Similarly, there is evidence that treatments might improve this sub-clinical inflammation, prevent new flares or decrease the risk of new flares in long-termfollow-up [15]. Current treatments for LTC include strategies such as daily emollient application, intermittent use of TAT (TAT-based strategy: once or twice a week [15–18]), avoidance strategies, dietary interventions, and immunosuppressive drugs.

‘Add-on’ therapies, which are superimposed on standard TAT, seem promising for LTC. Systemic immunosuppressants are used as LTC add-on treatments, but they are reserved for the most severely affected patients because of safety concerns. In addition, neither immunosuppressants nor other strategies (with the exception of desensitization) [19] have been evaluated in the long term. LTC is one of the most important core outcome domains to be targeted in AD trials according to the HOME (Harmonising Outcome Measures for Eczema) recommendations [20]. Safe add-on therapies, rigorously evaluated for disease LTC, are therefore needed.

Phototherapy is a good candidate for the ‘in-between’ AD population, being widely used as a second-line treatment in AD with demonstrated efficacy [12]. However, only short-term control has been evaluated, and only intensive schedules of two or three sessions per week have been tested and are used in current practice. A novel phototherapy regimen enabling a trade-off between disease control, ultraviolet (UV)-induced risks, and patient acceptability is required for LTC of the disease. No serious short-term adverse events were collected in the review by Garritsen et al. [12], where the most common adverse event was xerosis.

Vitamin D supplementation is another good candidate for the ‘in-between’ AD population, with several studies having shown lower serum levels of vitamin D to be correlated with more severe AD [21–26]. However, in these types of association studies, confounding factors such as solar exposure and socio-economic level, can be a major limitation. These observational studies are supported by some evidence that vitamin D could play a role in the different stages of AD pathogenesis [27, 28]. A meta-analysis on trials testing vitamin D supplementation yielded conflicting results, leaving its therapeutic efficacy undecided for short-term control and unknown for LTC [25].

We hypothesize that spaced-out phototherapy sessions during winter (exploratory trial) and vitamin D as an add-on therapy (main trial) could be beneficial to improve LTC of disease activity among AD patients.

## Methods/Design

### Objectives

Since both phototherapy and vitamin D supplementation are good candidates for LTC of disease activity in AD, we propose to study these two treatments jointly for the LTC of AD.

### Trial design

The study is a pragmatic, multicenter, national, randomized (1:1), superiority, crossover (two periods, two sequences) trial lasting 2 years (including two successive winters), and exploring add-on phototherapy versus observation in subjects receiving standard care (i.e., TAT). In the same population, we will be testing the LTC provided by oral supplementation of vitamin D versus placebo in a randomized, superiority, double-blind, parallel-group trial. Pragmatic trials [29] are the best-suited designs for studying add-on therapies in the context of long-term AD disease. The main pragmatic options are the following: recruitment in a primary care population, standard vitamin D supplementation, regimen not adapted to serum levels, strictly ‘as usual’ TAT use, and no recommendation on changes in lifestyle.

### Study setting

The study will be conducted in 16 French hospital centers with a network of primary care dermatologists in France.

### Participants and eligibility criteria

#### Inclusion criteria

Eligibility criteria: patients with AD (Hanifin and Rajka criteria), aged 15 or over, with > 2 years of disease evolution, moderate-to-severe disease (Investigator Global Assessment > 2), seasonality in disease severity (improvement in summer), and fewer than 100 previous phototherapy sessions in their lifetime. Eligible patients are to have received TAT for at least 12 weeks and to have symptoms requiring an intensification of the therapy, and they are to have easy access to a phototherapy cabin (widely available in primary care dermatology private practices in France).

#### Exclusion criteria

Exclusion criteria: patients with AD known to be aggravated by UV exposure; indication for a systemic immunosuppressant in the next 2 years; any cause of contra-indication for vitamin D supplementation: granulomatosis flare, primary hyperparathyroidism; clinical suspicion of hypercalciuria; any contra-indication for artificial or solar photo-exposure including genetic disease predisposing to skin cancer, any history of skin cancer (melanoma, squamous and basal skin cancers), lupus, dermatomyositis, any other photosensitizing skin disease, photosensitizing medication; and more than 100 previous phototherapy sessions in their lifetime.

### Interventions

Oral vitamin D supplementation will be administered at 100,000 IU, mono-dose (cholecalciferol, UVEDOSE^®^), every 3 months (standard guidelines) for 2 years. UVEDOSE^®^ is marketed by NextPharma LIMAY. The placebo of oral vitamin D supplementation is developed and marketed by NextPharma LIMAY.Phototherapy: the NB-UVB regimen will include a period of escalation of 3 weeks (three sessions per week for 3 weeks) and after that every 2 weeks for 6 months in total (winter: October to March). For phototype II–III, NB-UVB is initiated at 0.2 J/cm^2^ per session and is increased in increments of 0.1 from session to session up to the ninth session. For maintenance (every 2 weeks), we will continue with the dosage of the ninth session (1.0 or 1.1 J/cm^2^). The dosage can be altered according to clinical tolerance. For phototype IV–V, NB-UVB is initiated at 0.3 J/cm^2^ per session and is increased in increments of 0.1 from session to session up to the ninth session. For maintenance (every 2 weeks), we will maintain the exposure level of the ninth session (1.1 or 1.2 J/cm^2^). The exposure can be altered according to clinical tolerance.

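### The second of each pair of NB-UVB maintenance doses cannot be reached by the protocol's own escalation rule, and nothing says how to choose between the two

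*Protocol article*

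**What the plan says.** Everything relevant is in one place, the Interventions section of the protocol article.

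- Escalation consists of "a period of escalation of 3 weeks (three sessions per week for 3 weeks"), that is, nine sessions. Sessions then take place every two weeks, to a total of six months.
- Lighter group: "For phototype II–III, NB-UVB is initiated at 0.2 J/cm^2^ per session". Darker group: "For phototype IV–V, NB-UVB is initiated at 0.3 J/cm^2^ per session".
- In both groups the dose "is increased in increments of 0.1 from session to session up to the ninth session".
- Maintenance in the lighter group: "we will continue with the dosage of the ninth session (1.0 or 1.1" J/cm²). Maintenance in the darker group: "we will maintain the exposure level of the ninth session (1.1 or 1.2" J/cm²).
- In each group a further, free-standing sentence allows the dose to be changed for clinical tolerance. It does not refer to the two bracketed figures.

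**The concern.** A fixed start, a fixed step and a fixed number of sessions determine one end value. The text nevertheless prints two ninth-session values for each phototype group and gives no rule for choosing. The same 0.1 J/cm² gap appears in both groups, in separately worded sentences. That makes an isolated slip of the pen less likely and points to a miscounted step or an unstated choice.

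What is at stake is the definition of the experimental intervention from the fourth week to the end of the treated winter. The Background presents the regimen as a trade-off between disease control, UV-related risk and acceptability, so the dose is part of what is being tested. Treatment can be given by primary care dermatologists attached to 16 centres, so many operators apply the instruction. The primary model in Statistical methods codes phototherapy as given or not given, so it would not show a difference in dose between sites.

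**Working it through.** **Inputs, all from Interventions.** Number of escalation sessions: 3 per week × 3 weeks = 9. Start: 0.2 J/cm² (II–III) or 0.3 J/cm² (IV–V). Step: 0.1 J/cm² from one session to the next, ending at session nine.

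**Formula.** Dose at session k = start + (k − 1) × 0.1. Session nine therefore carries eight steps.

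**Attempt to reproduce the stated figures.**

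| Group | Sessions 1 to 9 (J/cm²) | Session 9 by the rule | Next step (would be session 10) | Stated for session 9 |
|---|---|---|---|---|
| II–III | 0.2, 0.3, 0.4, 0.5, 0.6, 0.7, 0.8, 0.9, 1.0 | 0.2 + 8 × 0.1 = 1.0 | 1.1 | 1.0 or 1.1 |
| IV–V | 0.3, 0.4, 0.5, 0.6, 0.7, 0.8, 0.9, 1.0, 1.1 | 0.3 + 8 × 0.1 = 1.1 | 1.2 | 1.1 or 1.2 |

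The lower figure of each pair reproduces exactly. The upper figure does not. To reach it, one of the inputs would have to differ:

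- nine steps instead of eight;
- a start 0.1 J/cm² higher (1.1 − 0.8 = 0.3; 1.2 − 0.8 = 0.4);
- a step of 0.1125 J/cm² ((1.1 − 0.2)/8 = (1.2 − 0.3)/8 = 0.1125).

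The text states none of these.

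**Size per maintenance session.** 0.1/1.0 = 10% (II–III) and 0.1/1.1 = 9.1% (IV–V).

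**Size per winter.** The article does not give the number of maintenance sessions. Taking six months as 26 weeks (an assumption), (26 − 3)/2 = 11.5, so 11 to 12 sessions. The excess is then 11 × 0.1 = 1.1 to 12 × 0.1 = 1.2 J/cm².

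The escalation totals under the rule are 5.4 J/cm² (II–III, nine sessions averaging 0.6) and 6.3 J/cm² (IV–V, nine sessions averaging 0.7). Adding maintenance gives:

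| Group | Maintenance sessions | Lower figure throughout (J/cm²) | Upper figure throughout (J/cm²) | Difference |
|---|---|---|---|---|
| II–III | 11 | 5.4 + 11 × 1.0 = 16.4 | 5.4 + 11 × 1.1 = 17.5 | +6.7% |
| II–III | 12 | 5.4 + 12 × 1.0 = 17.4 | 5.4 + 12 × 1.1 = 18.6 | +6.9% |
| IV–V | 11 | 6.3 + 11 × 1.1 = 18.4 | 6.3 + 11 × 1.2 = 19.5 | +6.0% |
| IV–V | 12 | 6.3 + 12 × 1.1 = 19.5 | 6.3 + 12 × 1.2 = 20.7 | +6.2% |

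These are upper bounds, because they use the higher figure at every maintenance session. They also assume that the nine escalation sessions are given as written.

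**The case against.** The strongest reply is that the instruction itself has only one value. Maintenance is defined as the dose of session nine, and the figures in brackets only illustrate it. A site that escalates as written and carries the ninth dose forward gives one dose per group. This stands as far as it goes. A reader might infer that sites must end up on two different doses, and the document does not support that: the divergence arises only where someone works from the bracket instead of the rule. The full protocol used at sites is not shown either.

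A reader might also infer that none of the stated maintenance doses follow from the rule. That is too strong, since the lower figure of each pair does.

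A second reply is that the dose may be altered for tolerance in a pragmatic trial, so a uniform dose was never promised. That is true, and some variation between patients is planned. But the tolerance sentence comes after the pair, is open-ended and is not linked to it, so it does not explain why session nine should have two values.

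Third, there is no inferential damage. Phototherapy is compared with observation within patients in a crossover, and randomization is stratified by clinical site, so a dose difference of 0.1 J/cm² between sites would not confound that comparison. This stands in full.

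Finally, a reader who notices that doses are given only for phototypes II–V might infer that eligible patients of other phototypes have no dosing rule. The article does not establish this. The exclusion for contra-indications to photo-exposure is open-ended and may cover some of these patients, and dosing for further phototypes may be in the full protocol. It is not part of this point.

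**Conclusion.** The inconsistency is real and can be checked from one paragraph. In each phototype group the upper stated ninth-session dose disagrees with the stated start, step and session count, and the text gives no criterion for using it. Condensation into an article does not account for this, because two printed statements disagree; nothing is merely left out.

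The consequence is modest. Where the bracket is followed at its upper figure, the excess is 0.1 J/cm² per maintenance session and no more than about 6–7% of cumulative winter exposure. This rests on the assumed 26-week winter with 11–12 maintenance sessions, on unaltered escalation, and on no tolerance adjustments. The point concerns how clearly and reproducibly the intervention is defined. It does not touch alpha, power or sample size. That the lower figures match the rule is arithmetic only and says nothing about which dose was meant.

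**What to change.** Within each phototype group, make the start dose, step, number of escalation sessions and stated ninth-session dose agree. If two maintenance values are intended, state what decides between them. The clinical team must settle which figure or which part of the rule is meant; the statistical review takes no position on it.

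The cost is one corrected sentence per phototype group and a note to sites. Trial status describes recruitment as ongoing, so the note could still reach operators before later treated winters. The analysis model and the sample size need no change.

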### Outcomes

#### Primary outcomes

The primary outcomes are (1) repeat measures of the Patient-Oriented Severity of Atopic Dermatitis Index (PO-SCORAD) severity score over 1 year and (2) cumulate consumption of TAT (number of tubes) during the winter; the outcomes will be tested following a hierarchical testing procedure. The choice of a patient-related score as the primary outcome will enable the capture of more data points without increasing the number of visits, and it is also coherent with the pragmatic design of the study.

#### Secondary outcomes

The secondary outcomes are repeat measures over 2 years for investigator-based severity scores (Eczema Area and Severity Index, Severity of Atopic Dermatitis Index, Investigator Global Assessment); patient-reported severity and quality of life scores (Patient-Oriented Eczema Measure, Dermatology Life Quality Index); serum vitamin D levels (25-(OH)-vitamin D); total IgE serum levels; weeks of satisfactory control; inter-visit cumulate consumption of TAT; and synthetic patient-reported satisfaction at the end of each winter.

Our trial includes all the recent core domains cited in the HOME recommendations [20].

### Recruitment

Particular attention will be given to recruiting a primary care population. Each region is organized from a university-based dermatology department into several ‘field study sites’ gathering several participating primary care dermatologists.

Meetings will be organized with primary care dermatologists to invite them to participate and to inform them on how the study will unfold. A trained study nurse will help them check their patients’ eligibility and plan the visits. The patients will have the possibility of receiving their phototherapy with their primary care dermatologist; scheduled visits will take place every 6 weeks.

### Sample size

We used the General Linear Multivariate Model Power & Sample Size (GLIMMPSE) software [30] to calculate the sample size for a repeat measure analysis with a desired power of at least 80%, a Type I error set at 0.05, and equal group sizes. The main predictor variable is phototherapy (yes or no) and the response variable is numerical (PO-SCORAD). Repeat measures are described as follows: 10 to 12 measures with time as the unit, and an equal distance between repeat numerical measures (every 4 weeks); we entered means for each time according to an anticipated evolution over time, and standard deviations of the response variable were set at 18. GLIMMPSE currently assumes that the standard deviation is constant across repeat measures. As we have some uncertainty about what standard deviation value to use, we used alternative values for variability and computed power for half the variance, the variance as specified, and twice the variance; this was also applied to means. GLIMMPSE automatically combines the sources of correlation into a final covariance matrix using a structured correlation based on the linear exponential auto-regressive model. The model describes a correlation that decreases monotonously with the distance between measures; the base correlation is set at 0.6 and the decay rate at 0.05. It can be noted that the minimum clinically significant difference for the PO-SCORAD score is indeed around 9, but we adopted a stance enabling the detection of a smaller difference, which means we are in an even better position to detect a clinically relevant difference.

We considered a main effect hypothesis test for the effect of a single predictor variable averaged across all other factors. We used the Hotelling–Lawley trace as the recommended statistical test for this kind of design, with a simple ‘between’ hypothesis and a complex ‘within’ hypothesis. We indeed plan to use a mixed model for our data analysis, and we will use the Wald test with Kenward–Roger degrees of freedom. It can be noted that the Hotelling–Lawley trace test for the general linear multivariate model coincides with the Wald test for the general linear mixed model.

On the basis of the sample size simulation (Additional file 1), we chose a total sample size of 340 subjects. This calculation was performed on the basis of a parallel-arm design; thus, using a crossover design, we considered we could halve the sample size. The assumption of no carry-over effect is allowed when planning a sample size for a crossover trial. For an intervention only in winter, we considered carryover would be minimized by design. Using a uniform and balanced crossover design, the treatment difference will not be aliased with sequence or period effects. However, an interaction of time and treatment should be taken into account, as we anticipate this could occur.

Power considerations in the area of repeat measures, crossover design and interaction between time and treatment are not straightforward. We therefore used GLIMMPSE, as for a two-arm trial. We realize that halving the sample size could appear simplistic and we therefore compared the sample size calculations between (1) a two parallel arm trial and (2) a crossover trial, considering only the last measure as the outcome, to check that the sample size reduction was not too optimistic. Finally, anticipating that 10–15% of patients will not complete the entire study (two 1-year sequences), the planned number of subjects to be enrolled is set at 200.

